# A hybrid design testing a 3-step implementation model for community scale-up of an HIV prevention intervention in rural Malawi: study protocol

**DOI:** 10.1186/s12889-018-5800-3

**Published:** 2018-08-02

**Keywords:** HIV prevention, Implementation science, Peer group intervention, Malawi, Community implementation, Community participation, Adult, Adolescent

## Abstract

**Background:**

Scaling-up evidence-based behavior change interventions can make a major contribution to meeting the UNAIDS goal of no new HIV infections by 2030. We developed an evidence-based peer group intervention for HIV prevention and testing in Malawi that is ready for wider dissemination. Our innovative approach turns over ownership of implementation to rural communities. We adapted a 3-Step Implementation Model (prepare, roll-out and sustain) for communities to use. Using a hybrid design, we simultaneously evaluate community implementation processes and program effectiveness.

**Methods:**

Three communities in southern Malawi begin implementation in randomly-assigned order using a stepped wedge design. Our evaluation sample size of 144 adults and 144 youth per community provides sufficient power to examine primary outcomes of condom use and HIV testing. Prior to any implementation, the first participants in all three communities are recruited and complete the Wave 1 baseline survey. Waves 2–4 surveys occur after each community completes roll-out. Each community follows the model’s three steps. During Prepare, the community develops a plan and trains peer group leaders. During Roll-Out, peer leaders offer the program. During Sustain, the community makes and carries out plans to continue and expand the program and ultimately obtain local funding. We evaluate degree of implementation success (Aim 1) using the community’s benchmark scores (e.g, # of peer groups held). We assess implementation process and factors related to success (Aim 2) using repeated interviews and observations, benchmarks from Aim 1 and fidelity assessments. We assess effectiveness of the peer group intervention when delivered by communities (Aim 3) using multi-level regression models to analyze data from repeated surveys. Finally, we use mixed methods analyses of all data to assess feasibility, acceptability and sustainability (Aim 4).

**Discussion:**

The project is underway, and thus far the first communities have enthusiastically begun implementation. We have had to make several modifications along the way, such as moving from rapid-tests of STIs to symptoms screening by a nurse due to problems with test reliability and availability. If successful, results will provide a replicable evidence-based model for future community implementation of this and other health interventions.

**Trial registration:**

Clinical Trials.gov NCT02765659 Registered May 6, 2016.

## Background

Addressing HIV transmission in low-resource countries in sub-Saharan Africa is essential to meeting the UNAIDS 2030 goal of no new HIV infections [1]. Although new infections continue to decline, there were 1.8 million new infections globally in 2016, and 64% of these occurred in sub-Saharan Africa [2]. Nearly 40% of new infections occur among young people ages 15–24. Scaling-up evidence-based behavior change interventions can help prevent new infections by reducing knowledge gaps and risky sexual behaviors and increasing early testing and treatment.

Our research team developed an evidence-based behavior change intervention for HIV prevention and testing in rural Malawi, an African country hard hit by the HIV epidemic. This 7-session peer group intervention, called *Mzake ndi Mzake* (Friend-to-Friend, *Mzake*), is guided by Bandura’s social-cognitive learning theory [3] that emphasizes building self-efficacy, which has been linked with efficacy in previous meta-analyses and reviews [4–9]. Each session incorporates games and role-plays that rehearse specific steps needed for HIV prevention, such as discussing condom use with a partner. Importantly, the intervention is designed for all reproductive aged individuals regardless of age or gender. Using a quasi-experimental design, we compared a random sample of adults and youth in communities that received *Mzake* and control communities. People in the *Mzake* communities reported significantly more HIV prevention behaviors, including more condom use (Adults, 25% vs. 12%; Youth, 70% vs. 49%) and more HIV tests within the past year (Adults, 18% vs. 10%; Youth, 14% vs. 7%) [10–12].

With efficacy established, this intervention is ready for wider dissemination to other rural communities in Malawi. In the efficacy study, volunteer health workers served as peer leaders and provided training. However, persistent health worker shortages mean that Malawi’s health system does not have the capacity to lead community scale-up because they must meet expanding demands for HIV testing and treatment as well as other health needs.

We opted to use a promising alternative to reach rural communities – community ownership and leadership of scale-up of this evidence-based HIV prevention intervention. This approach falls within the broad framework of community-based participatory research (CBPR), where the agenda is set collaboratively by the community and researchers [13–17]. Numerous studies have documented that a participatory approach integrating the perspectives and interests of community leaders and members, researchers and other stakeholders enhances effectiveness and sustainability [18]. We chose to bring the intervention to Phalombe district in southern Malawi, where the need for HIV prevention is especially great. HIV prevalence in the Southern Region is 16%, twice that of other regions in Malawi (MPHIA 2016) [19], and Phalombe is a low-resource, rural district that has received few HIV prevention initiatives.

### Preliminary work prior to funding

The first step in testing this CBPR alternative was to determine if local communities were ready to take up the challenge and identify what they would need to do so. We met with local leaders and community members, described the intervention, and discussed their willingness to take on *Mzake*’s implementation. All were enthusiastic about introducing HIV prevention in their communities. One leader observed that the HIV epidemic continues to hurt families and said, *“None of us are spared from the agony of losing many loved ones …. We would do anything possible to support the study … for everyone to benefit from it.”* Leaders noted that they could use same strategies and resources they now use to organize local traditions and church or volunteer activities but would need to acquire appropriate health knowledge and program-specific implementation skills. One leader observed, *“We have heard about prevention messages on the radio, in meetings, through drama and on the national day for HIV prevention. But when we go home we really do not understand how we can get our people protected.”* These community discussions led to the development of a local multi-sectoral partnership with communities at the center that ensured their ongoing access to local support and resources. The District Commissioner (head of district government) agreed to integrate this program into their district agenda and resource allocation. The district’s health team agreed to contribute health knowledge, local statistics and training support. The research team agreed to provide guidance for implementation and *Mzake* program-specific knowledge. Traditional leaders at all levels agreed to help mobilize communities and disseminate progress.

To move forward, we needed a simple but effective implementation model that communities could easily use as they took ownership of the *Mzake* program and rolled it out. Most implementation models are developed for use by researchers and health professionals in clinical settings [20]. These were too complex and abstract for community use. The model needed to be accessible to individuals with less education and little exposure to formal research. An evidence-based model originally used to implement a hospital-based intervention in South Africa was the most appropriate because it had been used successfully in Africa with clinical staff, some of whom had relatively low education [21–24]. In consultation with [name], one of the model’s original developers, we adapted this model for community use. We simplified it by reducing the model from six to three major steps: *prepare, roll out and sustain.* We also developed *Mzake*-specific benchmarks for each step; the benchmarks guide implementation and are also used by communities to document their progress.

The purpose of this research is to test whether three rural communities in Phalombe, Malawi can successfully implement the *Mzake* intervention using our simple 3-Step Implementation Model. The specific aims are to:Prepare and support three communities as they use the 3-Step Model to implement the *Mzake* peer group intervention to reduce new HIV infections.Identify implementation patterns across sites and over time using mixed-methods analyses.Assess *Mzake* effectiveness when implemented by communities.Hypothesis: At each wave, participants who have completed the program will have significant improvement in HIV-related behavioral outcomes and sexually transmitted infections (STIs) compared to those in communities where the intervention has not yet been introduced.Evaluate whether the 3-Step Model is feasible, acceptable, effective and sustainable when used by communities to implement an evidence-based intervention.

Results of this study will make a major contribution to health promotion policy and to implementation science. If communities can take the lead in scaling-up evidence-based interventions to reduce new HIV infections, this will offer a new approach to scaling up HIV prevention without overburdening the health system. If our simple 3-Step Model helps community members achieve this, the model and lessons learned about its use in three different communities will make important empirically validated contributions to implementation science.

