## Methods

### Design

This study uses a hybrid design, which was developed to advance implementation science by examining both implementation processes and effectiveness in a single study [25, 26]. We give equal attention to both processes and effectiveness evaluation, a balanced design recommended where there is already evidence supporting efficacy [25].

We use a stepped wedge design to evaluate effectiveness, with staggered introduction of the intervention in three communities in randomly assigned order (Fig. 1). The stepped wedge design [27–29] has the advantage that all groups receive the intervention, which is ethically important, especially in a community intervention. This design is efficient because the repeated measures allow participants to serve as controls until the intervention is introduced in their community. In each community, the first 144 adults and 144 youth are asked to both receive the intervention and to participate in the effectiveness evaluation. Outcome measures are assessed at baseline and after each community rolls out the intervention.

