#### Power analysis, Aim 2 effectiveness

We performed a power analysis for the stepped wedge effectiveness component to determine sample size. Conventional power calculation programs are not able to consider both the intra-class correlation (ICC) for the intervention clusters, and the ICC for repeated measures of individuals over time. Therefore, we performed 1000 simulations using the stepped wedge design, for both continuous outcomes (analyzed using mixed-effects regression) and binary outcome (analyzed using mixed-effects logistic regression) [31, 32]. We conservatively set cluster-level ICC to be 0.10, based on two previous community or classroom studies that found an ICC of 0.05 [33, 34]. Individual-level ICC was set to range from 0.2 to 0.4, as is typical for correlations between repeated measurements of an individual. We set retention rates at 85, 80, and 75% at waves 2 through 4, a conservative estimate given our prior study with 80% retention at 18 months. Expected effect sizes (0.10 to 0.20 for continuous outcomes; odds ratios ranging from 1.2 to 2.2 for dichotomous outcomes) were based on significant outcomes in our previous efficacy study [10, 11] or, for comprehensive HIV knowledge and sexually transmitted infection (STI) prevalence, a 2010 national survey [35]. With 80% statistical power, the sample of 432 persons (youth or adults) with retention rates of 75% at the last wave, supported a minimum detectable effect size of 0.13 for continuous outcome variables, and a minimum detectable odds ratio of size 1.36. Thus, we have sufficient power to detect all expected intervention effects for outcome variables for adults and youth separately.

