*Sustaining* is divided into two periods, 11 months of sustaining with partial support, followed by independent sustaining up to the last year of the grant period. Because of the staggered implementation plan, Site 1 will have 30 months of independent sustaining, Site 2 will have 18 months and Site 3 will have 8 months of independent sustaining. During sustaining with support, sites are told that they will receive a specific amount of money for 11 months of sustaining activities. The committee members receive advanced training regarding sustaining and discuss their vision for what should happen. They receive additional guidance on planning activities, budgeting for them and accounting for expenditures. Activities during sustaining include training more peer group leaders and possibly new committee members, holding *Mzake* groups for new participants and in new areas, and booster activities for those who have already attended *Mzake*. One important part of sustaining is ensuring the capacity to train new peer group leaders, and the committee may decide to ask for training of interested peer leaders as trainers. They then decide how to allocate their efforts and carry out their plans, monitoring what is happening and making any needed adjustments. Toward the end of sustaining with support, the committee learns how to write a proposal and budget in a workshop and seeks funding from us and other sources. Our staff is available but does not initiate regular contacts as we do during roll-out.

During independent sustaining, the community should begin to expand to new areas and obtain new support for their work. They can apply to us for a small grant and to the District Commissioner’s office and other funders for additional months of partial funding. The Study Team continues “hands-off” observation of progress during the remainder of this period [23]. The intention is for each community to continue indefinitely. However, we only observe progress up to Month 52. *The primary capacities built during this period are independently training new peer leaders, conducting booster sessions, expanding to new parts of their own site and possibly to other sites, maintaining financial records, and preparing proposals and budgets to sustain activities.*

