#### Aim 3 (effectiveness analysis)

The effectiveness of the *Mzake* intervention when offered by communities is determined by survey data and STI symptom interviews with a nurse at Waves 1–4. We will complete a CONSORT diagram showing recruitment, retention and loss to follow-up at each wave. We then examine significant factors associated with lost to follow-up. Identified attrition factors will be controlled in later analyses.

To evaluate the effectiveness of the intervention in improving HIV-related outcomes, we will use multi-level mixed-effects regression (for continuous outcomes) and logistic regression (for dichotomous variables) models [51]. These methods allow us to take into account time of implementation as well as lack of independence among repeated measurements and members of the same peer group. The hierarchical structure of the data is conceptualized as repeated outcome measures (level 1), nested within individuals (level 2) and nested within peer groups (level 3). Random individual and peer group effects will account for correlations between repeated measurements and between individuals from the same peer group. Intervention condition will be a time-varying covariate that reflects the stepped-wedge design in which individuals receive intervention at different stage of the study. Site and demographic factors (both individual level and community level) will be treated as fixed-effects covariates to account for differences. Time trend interactions for intervention and imporant factors will be tested to identify differential effects over time. Youth and adult data will be analyzed both together and separately. Model selections for the number of random effects and the variance-covariance structures for the outcome variables will be performed using likelihood ratio tests. Backward selection will be employed for the fixed effects. *Aim 3 analysis identifies effectiveness overall and by site.*

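### The Aim 3 hypothesis contrasts programme completers with not-yet-reached communities at each wave, which is neither available at Wave 4 nor randomised, and differs from the planned pooled model

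*Protocol article*

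**What the plan says.** The specific aims at the end of the Background give one hypothesis for effectiveness: "At each wave, participants who have completed the program will have significant improvement in HIV-related behavioral outcomes" (and in sexually transmitted infections), "compared to those in communities where the intervention has not yet been introduced".

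The Design section describes "staggered introduction of the intervention in three communities in randomly assigned order". The timing of the surveys is in the abstract: "Prior to any implementation, the first participants in all three communities are recruited and complete the Wave 1 baseline survey", and "Waves 2–4 surveys occur after each community completes roll-out".

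The Aim 3 analysis section plans multi-level mixed models over repeated measures, with site as a fixed effect and random effects for individuals and peer groups. Exposure enters as follows: "Intervention condition will be a time-varying covariate that reflects the stepped-wedge design in which individuals receive intervention at different stage of the study". The survey row of Table 1 records the number of sessions attended as a dose measure. The article does not define completion.

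**The concern.** The hypothesis and the model describe different quantities. The hypothesis has two features that the design cannot support.

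- **Wave.** It promises a comparison at every wave with communities still waiting. At the last wave none is waiting.
- **Population.** One side is people who finished the programme; the other is everyone enrolled in the waiting communities. Participants on both sides volunteered at Wave 1, so volunteering itself is balanced. Completing seven sessions is a later choice that the waiting participants have not yet faced, and randomising the order of communities does not balance it. If people who finish already tend towards safer behaviour, the contrast favours the programme.

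The model could settle this, but its phrase about individuals receiving the intervention can mean the community's step or the person's own attendance. The hypothesis covers both primary outcomes (safer sex practices and HIV testing). Left open, the choice between the two codings could be made after the data are seen.

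**Working it through.** **1. Where the stated contrast exists.** There are three communities with 144 adults and 144 youth each. Retention in the Power analysis section is 85, 80 and 75% at Waves 2 to 4. Per age group:

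| Wave | Communities reached v not reached | Expected n |
|---|---|---|
| 1 | 0 v 3 | 0 v 432 |
| 2 | 1 v 2 | 144 × 0.85 = 122 v 288 × 0.85 = 245 |
| 3 | 2 v 1 | 288 × 0.80 = 230 v 144 × 0.80 = 115 |
| 4 | 3 v 0 | 432 × 0.75 = 324 v 0 |

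The site timeline agrees: "Site 1 will have 30 months of independent sustaining, Site 2 will have 18 months and Site 3 will have 8 months". With equal step lengths and a common end, starts are 30 − 18 = 12 and 18 − 8 = 10 months apart, while prepare plus roll-out takes 2 + 8 = 10 months. Waiting communities therefore exist at Waves 2 and 3 and not at Wave 4. Wave 1 is a baseline, so its lack of completers is only loose wording.

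**2. The plan's own power figure.** The Power analysis section gives a minimum detectable effect of 0.13 for "the sample of 432 persons (youth or adults) with retention rates of 75% at the last wave". I computed the generalised least squares variance of the exposure effect for rows 0111, 0011, 0001 over four waves, with cluster ICC 0.10, individual ICC 0.2 to 0.4 and the stated retention. The minimum detectable effect is (1.96 + 0.84) × SE; the two-sided 5% level is my assumption, as none is stated. Without wave effects the result is 0.115 to 0.144, which brackets 0.13. With wave effects it is 0.195 to 0.250. The 0.13 therefore belongs to a pooled analysis and says nothing about single waves.

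**3. A single-wave contrast.** The formula is 2.80 × √(1/n₁ + 1/n₂), in SD units.

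- Wave 2: 2.80 × √(1/122.4 + 1/244.8) = 0.31.
- Wave 3: 2.80 × √(1/230.4 + 1/115.2) = 0.32.

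With 12 groups per age group and site, a group has 144/12 = 12 members, of whom 10.2 and 9.6 are retained. If ICC 0.10 applies to peer groups, the design effects are 1 + 9.2 × 0.10 = 1.92 and 1 + 8.6 × 0.10 = 1.86.

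- Wave 2: 0.31 × √1.92 = 0.43.
- Wave 3: 0.32 × √1.86 = 0.44.

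These counts include everyone retained; completers alone are fewer. The plan expects effects of 0.10 to 0.20.

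**4. Completer selection with no true effect (illustration).** Let p be the prevalence among all enrolled, c the share completing, and θ the odds ratio between the safer behaviour and completing. Completers (p₁) and non-completers (p₀) satisfy c·p₁ + (1 − c)·p₀ = p and odds(p₁)/odds(p₀) = θ. The spurious odds ratio is odds(p₁)/odds(p). Values of p come from the efficacy study's control communities as cited in the Background (10% adult testing, 12% adult and 49% youth condom use). Values of c (0.6 to 0.9) and θ (1.2 to 2.0) are assumed.

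- p = 0.10, c = 0.9, θ = 1.2: odds ratio 1.02.
- p = 0.10, c = 0.7, θ = 2.0: p₁ = 0.116, odds ratio about 1.18.
- p = 0.49, c = 0.6, θ = 2.0: p₁ = 0.558, odds ratio about 1.32.

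The plan's expected odds ratios run from 1.2 to 2.2, and its detectable odds ratio is 1.36.

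**The case against.** The sentence is an aim, and the analysis is elsewhere. The Aim 3 section specifies one pooled model with a time-varying condition, no wave-by-wave tests and no completer-only analysis set. A final wave with everyone exposed is normal in a stepped wedge, and the Design section lets participants act as controls until their own community starts, so earlier waves also supply control information. The phrase about individuals receiving the intervention reads most naturally as the site's step, and detailed coding rules often sit in an analysis plan not shown here. All of this stands as a defence of the model. It does not repair the hypothesis, which names a different population and a comparator absent at Wave 4.

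It can also be said that the hypothesis speaks of improvement, so baseline values would help. They would, modestly: at a repeated-measures correlation of 0.4, baseline adjustment multiplies the unclustered 0.31 by √(1 − 0.16) = 0.92, giving 0.28, still above 0.20. Individual random effects would likewise absorb part of any stable difference between completers and others, so the odds ratios above describe an unadjusted contrast. They would not remove selection linked to changes after enrolment.

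Two stronger readings are tempting. One is that single-wave contrasts could detect only about 1.1 SD: √(0.10 × (1 + 1/2)) = 0.39, times 2.80. That places the whole ICC of 0.10 between communities. The Power analysis section speaks only of intervention clusters, and the Aim 3 model has peer groups as its third level with site fixed. The other is that the hypothesis can be neither confirmed nor refuted. Waves 2 and 3 do offer the contrast, though weakly, and the pooled model is estimable.

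**Conclusion.** The point holds as a conflict within the protocol. The stated hypothesis sets completers against all participants in waiting communities at each wave, but Wave 4 has no waiting community, and completion was not randomised. The planned model estimates something else, and its wording leaves the exposure coding open.

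The Wave 4 point follows directly from the survey timing. The direction of the selection bias is an inference, and its size (odds ratio about 1.02 to 1.32) rests on assumed completion rates and associations; the upper part of that range overlaps the low end of the expected effects but stays below 1.36. The single-wave figures of 0.31 to 0.44 SD rest on an assumed two-sided 5% level and on how clustering is treated. They show that the stated power does not carry over to a claim at each wave. They do not show that the planned analysis fails. A reader should not conclude that the stepped-wedge design or the pooled model is invalid.

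**What to change.** Restate the Aim 3 hypothesis along these lines: among all participants enrolled at Wave 1, regardless of sessions attended, outcomes are better when their community is in its assigned post-roll-out condition than when it is not, estimated in one model over Waves 1 to 4 with wave and site effects. In the Aim 3 analysis, state that intervention condition is coded from the community's assigned roll-out step. Keep sessions attended or completion as a secondary dose analysis, with completion defined and the result read as an association.

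Wave 1 must stay in the model because it is the first community's only unexposed wave. With equal cells and site and wave effects, the residual sum of squares of exposure is 3 − 0.5 − 1.667 = 0.833 over Waves 1 to 4, and 2 − 0.667 − 0.667 = 0.667 over Waves 2 to 4. Dropping Wave 1 would therefore raise the standard error by √(0.833/0.667) − 1, about 12%.

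The cost is one sentence and one coding rule; attendance is already collected. The estimated effect may be smaller than among completers. The power statement should be checked against the model with wave effects, since 0.13 was reproduced only without them.
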